**Title: Efficacy and cost effectiveness of malaria diagnosis procedures and the rational use of ACT in Zanzibar**

**Acronym: ZRDT**

**Updated on:** January,2005

**Design**: Multi center comparative validation study

**Study** **sites**: Muyuni, Uzini, Kinyasini and Mzambarauni PHCU’s, Unguja & Pemba Islands

# List of abbreviations

ACT Artemisinin Combination Therapy

AL artemether-lumefantrine (Coartem®)

ASAQ artesunate + amodiaquine

CMM Morbidity Mortality Cohort Study

CRF Case Record Form

HF Health facilities

HLSO Health Laboratory Scientific Officer

IPT Intermittent Presumptive Treatment

ITN Insecticide treated nets

KI Karolinska Institutet

MD Medical Doctor

MLT Medical Laboratory Technician

MOHSW Ministry of Health and Social Welfare

MSF Medecins Sans Frontieres

PPV Predictive Positive Value

PNV Predictive Negative Value

Q quinine

RDT Rapid Diagnostic Test

SP sulphadoxine-pyrimethamine

WHO World Health Organization

ZAMRUKI Zanzibar Malaria Research Unit Karolinska Institutet

ZHRC Zanzibar Health Research Council

ZMCP Zanzibar Malaria Control Programme

ZMoHSW Zanzibar Ministry of Health and Social Welfare

# Introduction

The spread and intensification of antimalarial drug resistance has forced many countries in Sub-Saharan Africa to monitor or change their treatment policies. Zanzibar is implementing Artemisinin based Combination Therapy (ACT) for the treatment of *P. falciparum* malaria since September 2003. The first line drug for uncomplicated malaria in this new policy is artesunate +amodiaquine (ASAQ), and the second line is artemether-lumefantrine ((AL) Coartem®) - quinine (Q) remains the first line drug for treatment of severe malaria.

Although showing increasing failure rates, sulphadoxine-pyrimethamine (SP) is, for reasons of safety, currently the only available alternative for Intermittent Presumptive Treatment (IPT) and therapeutic treatment during pregnancy.

Malaria is the leading public health problem in terms of morbidity and mortality in the Isles. More than 60% of patients presenting at

Government public health facilities are diagnosed as malaria cases. Due to a shortage of resources such as microscopes, electricity, reagents and laboratory practitioners, an estimated 90% of all malaria treated cases in the public health system are based on clinical diagnosis alone. Furthermore, according to a recent ACT effectiveness study (CMM-study, ZAMRUKI), this practice results in an over diagnosis/treatment of malaria exceeding 50%.

There are so many factors which facing developing countries on setup of Malaria microscopy, such as expensively of equipment and reagents and the number of laboratory practitioners is limited in the Isles. However, with the introduction of ACTs the optimization of malaria diagnosis and the rational use of these more expensive new drugs are considered of high importance. Theoretically, accurate malaria diagnosis should reduce the number of patients unnecessarily treated with antimalarials and the number of patients returning to the health facilities because of misdiagnosis, thus reducing the cost of treatment and, equally important, minimizing the potentially resistance driving selection pressure on the parasites.

MSF is currently implementing a malaria project in the South and North A district of Unguja and Wete district of Pemba, Zanzibar. The aim of the project is to improve clinical malaria case management by using ACT in combination with RDT aided diagnosis in health facilities which have no malaria microscopy.

In June 2004 MSF started an intervention in Unguja South and North A district and Wete district in Pemba within Zanzibar archipelago. The project aims at improving malaria case management; supporting the implementation of the new therapy (arteminsin + amodiaquine) and improving the management of anaemia, lower acute respiratory infections and diarrhoea among under 5 year-old children. The time framework is 18 months.

Nurses issue around 80% of the prescriptions delivered, clinical officers issuing the remaining 20%. When the prescribing person in charge is not present in the HF, non-medical staff members (hospital orderlies) carry out the consultation.

Checks of registration books in the health facilities within South District revealed that, since the new protocol started being implemented in September 2003, there had been a transitional period (from September 2003 to January 2004) when the treatment guideline was not followed consistently.

Rapid diagnostic Test (RDT), based on the detection of antigen derived from malaria parasites, represent a good alternative to microscopy for the diagnosis of *Plasmodium falciparum* malaria (WHO, 1966), in areas lacking resources such as electricity, trained laboratory practitioners and supplies of reagents.

The Para check Pf (dipstick and device) was considered as the most appropriate for the use in the field, being sensitive (97%), moderately specific (88%), easy to use and cheap (about US$ 0.5/test), *Guthmann et.al Trans. of the Royal Soc. TMH (2002) 96,254 -257*

The aim of this study is to evaluate the effect of RDT on the accurate malaria diagnosis and rational use of ACT.

## The malaria situation in Zanzibar

Malaria is a major public health problem in Zanzibar. The parasite prevalence in children between the ages of 2 to 11 years is considerable (up to 60 %). Malaria transmission is stable throughout the year. Resistance to chloroquine and sulfadoxine-pyrimethamine is approximately 60%, and 13% respectively.

# Study protocol

## Problem statement

Approximately 90% of all malaria cases are diagnosed in Public Health facilities, using a clinical approach based on signs and symptoms, resulting in an estimated over-diagnosis rate of 40-50%. With the relatively higher cost of ACT and the inherent risk of promoting resistance development by the resulting over-prescription, the cost effectiveness and reduction of overall antimalarial drug pressure expected by introducing RDT diagnosis needs to be scientifically documented.

## Study objective

The primary objective is to compare the proportions of malaria treatments prescribed between two cohorts of clinical diagnosis + RDT and clinical diagnosis alone*.*

Secondary objectives include evaluation of sensitivity, specificity, PPV and PNV of RDT, as well as cost benefit calculations based on reduction of both initial treatment and of revisits due to misdiagnosis.

The selection of the study sites will enable an evaluation of the impact of MSF case management intervention since two out of four sites will already have received “on the job training” on clinical diagnosis through MSF.

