### Duration of study

Each patient will spend approximately 1 hour at the study site. There will be a passive follow up period of a minimum of 14 days after the initial visit, during which any subsequent treatment will be evaluated if the patient is seen/examined at the site again. Depending on the rate of enrollment, which is expected to be 100 patients/week/site, the study will run for approximately 45 days in each site.

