4.4.2 Sampling for determining parasitemia

A few drops of blood will be taken from all enrolled patients to determine parasitemia: for confirmation of parasitemia by standard microscopy examination in central laboratory in clinical and for the RDT in the intervention arm. The results of RDT will be provided to the patients before treatment, but the microscopy results will only be available for study analysis purposes. Manufacturer’s Instructions Procedure and a special training session by study supervisor prior to study initiation will assist the study clinical officer to perform Rapid Diagnostic Tests. Blood films will be stained with 3% Giemsa for 30 minutes and asexual parasite density will be calculated by counting 200 white blood cells, assuming the white blood cell count of 8000/mm3. If less than 10 parasites are detected per 200 white blood cells, estimates will be made against another 500 white blood cells.

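### If the revisit component counts only returns put down to misdiagnosis, it would shrink in the RDT arm even if RDT changes nobody's chance of returning

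*Protocol*

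**What the plan says.** Section 4.2 (Study objective) gives the economic objective two inputs: "cost benefit calculations based on reduction of both initial treatment and of revisits due to misdiagnosis". The Introduction supplies the reasoning, as something expected in theory: accurate diagnosis should lower "the number of patients returning to the health facilities because of misdiagnosis, thus reducing the cost of treatment".

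On data capture, Duration of study provides a passive follow-up of at least 14 days in which "any subsequent treatment will be evaluated if the patient is seen/examined at the site again". Clinical assessment tells every patient to come back if symptoms persist or worsen, and in any case on day 14 or later for a final visit.

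Blood slides are taken from all patients in both arms and read centrally (Bioanalytical assays). Section 4.4.2 says that "the microscopy results will only be available for study analysis purposes".

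The protocol does not say how a return is to be attributed to misdiagnosis, nor does it state that other returns are ignored.

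**The concern.** A return can be put down to misdiagnosis only if the first diagnosis was wrong. How often that happens is what RDT is introduced to change. A count restricted in this way selects patients on something that happens after allocation and differs between the arms by design.

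The selection runs in one direction. A slide-negative, RDT-negative patient who is sent home without an antimalarial and returns still unwell was correctly diagnosed, so the return would not count, although the visit uses facility time all the same. The RDT arm should hold many more such patients. If they return more often, that is the offsetting cost a cost-benefit analysis has to see.

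At stake is a reported saving in revisits that would partly or wholly restate the improvement in diagnosis. Cost effectiveness is in the study title, and revisits are one of two stated inputs. The primary objective, the proportion prescribed malaria treatment, is not affected.

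**Working it through.** The protocol gives no figure for revisits or for the cost-benefit result, so there is nothing of its own to reproduce. The check asks what the restricted count shows when RDT has no effect on returning.

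**Inputs from the protocol**
- RDT sensitivity Se = 97% and specificity Sp = 88% (Introduction).
- Over-diagnosis d under clinical diagnosis (CD): 40-50% (Problem statement). The Introduction also gives a figure above 50%; 40-50% is used here.
- Share called malaria T: above 60% (Introduction). This is for all attenders at public facilities, whereas the study enrols patients with fever or compatible symptoms. T is therefore varied from 60% to 100%.

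**Assumptions**
- f, the share of malaria missed among those not called malaria under CD.
- RDT results always followed (relaxed below).
- The same return risk r for everyone, which is the no-effect case.

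**Formulas**
- Misdiagnosed under CD: M_CD = T·d + (1 − T)·f
- Slide prevalence: p = T·(1 − d) + (1 − T)·f
- Misdiagnosed under RDT: M_RDT = (1 − Se)·p + (1 − Sp)·(1 − p)
- Fall in counted revisits: 1 − r·M_RDT / (r·M_CD) = 1 − M_RDT / M_CD, so r cancels.

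| T | d | f | p | M_CD | M_RDT | Fall |
|---|---|---|---|---|---|---|
| 60% | 40% | 0 | 36% | 24% | 0.03×0.36 + 0.12×0.64 = 8.76% | 63.5% |
| 60% | 50% | 0 | 30% | 30% | 0.03×0.30 + 0.12×0.70 = 9.3% | 69% |
| 60% | 40% | 10% | 40% | 28% | 0.03×0.40 + 0.12×0.60 = 8.4% | 70% |
| 60% | 50% | 25% | 40% | 40% | 8.4% | 79% |
| 100% | 40% | – | 60% | 40% | 0.03×0.60 + 0.12×0.40 = 6.6% | 83.5% |
| 100% | 50% | – | 50% | 50% | 0.03×0.50 + 0.12×0.50 = 7.5% | 85% |

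**In counts.** With 824/2 = 412 patients per arm, an assumed r of 10% and T = 100%, all returns are 41.2 in each arm. The restricted count is 16.5-20.6 under CD and 2.7-3.1 under RDT.

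**Partial adherence.** Take T = 100% and let a share a of RDT-negatives still be called malaria. Then M_RDT = (1 − Se)·p·(1 − a) + (1 − Sp)·(1 − p) + Sp·(1 − p)·a.
- a = 10%: fall 75-77%.
- a = 20%: fall 67-68%.
- a = 50%, d = 40%: 0.009 + 0.048 + 0.176 = 0.233 against 0.40, a fall of about 42%. At d = 50%: 0.0075 + 0.06 + 0.22 = 0.2875 against 0.50, a fall of 42.5%.

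The 42% is not a floor. With fewer patients called malaria under CD the fall starts from a lower level, so the same departure would bring it lower.

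**The restricted count cannot tell an effect from none.** Suppose misdiagnosed patients return k times as often as others, in both arms alike. Then k cancels too, and the fall is again 1 − M_RDT / M_CD whatever k is. The comparison of all returns does respond, with a fall of 1 − [1 + (k − 1)·M_RDT] / [1 + (k − 1)·M_CD]. At T = 100% this is 0% for k = 1. For k = 2 it is 1 − 1.066/1.40 = 24% (d = 40%) to 1 − 1.075/1.50 = 28% (d = 50%).

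**The two measures can point in opposite directions.** Purely as illustration, take the fourth row of the table with assumed return risks of 8% if treated and 12% if untreated. Per 100 patients:
- All returns, CD: 60×0.08 + 40×0.12 = 9.6.
- All returns, RDT: 46×0.08 + 54×0.12 = 10.2.
- Restricted count, CD: 30×0.08 + 10×0.12 = 3.6.
- Restricted count, RDT: 7.2×0.08 + 1.2×0.12 = 0.7.

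In the RDT arm 60×0.88 = 52.8 of 100 patients are correctly untreated, and none of their returns would count.

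**The case against.** The strongest reply is that the protocol never prescribes this count. Section 4.2 does not say that other returns are excluded, the Introduction offers the phrase as a causal expectation, and Duration of study covers treatment at any return to the site. A comparison of all returns by arm fits those passages and shows no change when there is no effect. A reader might infer that the fall is forced by definition. The documents do not support that, because there is no attribution rule. This part of the reply stands, and the point is conditional for that reason.

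A related reply is that a return caused by misdiagnosis is not the same as a return by a misdiagnosed patient. If misdiagnosis has no effect on returning, it causes no returns in either arm. That is right in principle. But the cause of a single return cannot be observed, so a count faithful to the phrase would in practice classify returns by the first diagnosis. The causal quantity is reached by comparing all returns between arms, which is the fix.

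Three stronger readings should also be set aside:
- **That the whole cost-benefit outcome falls by these percentages.** It does not. Initial treatment is the other input and is untouched by this problem.
- **That site staff would attribute causes unevenly because they see a test result in one arm only.** The protocol does not say that staff do the attributing. Slides from all patients are read centrally, so one rule for both arms is feasible.
- **That total returns will rise under RDT.** The illustration rests on assumed return risks and shows only that the two measures can diverge.

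Finally, an analysis plan not shown here may define attribution. But a rule that kept to the wording of section 4.2 would put the restriction into practice, so the wording itself is worth changing.

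**Conclusion.** The point holds conditionally. Applied as worded, by counting returns of patients whose first diagnosis was wrong, the revisit component would fall by about 64-85% with RDT results followed, and by about 42% with all enrolled patients clinically called malaria and half of RDT-negatives still so called, even with no effect on returning. Only Se, Sp and the over-diagnosis range come from the protocol. The share called malaria, missed cases and adherence among enrolled patients are assumptions, so the size is indicative. The direction holds wherever RDT lowers the share misdiagnosed. The measure would restate diagnostic accuracy as a saving in visits and leave out the returns of correctly untreated patients. This is a flaw in how a secondary objective is worded, and it should be corrected before the cost analysis.

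**What to change.** In section 4.2, base the revisit component on all unscheduled returns to the site, for any reason, during the passive follow-up, per 100 enrolled and by arm of enrolment, and cost all of them. Exclude only the scheduled final visit on day 14 or later that every patient is told to make. A cut-off at day 14 would be too blunt: follow-up is at least 14 days, and later returns because of illness would be lost.

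Any split by misdiagnosis should be descriptive, assigned centrally from the day-0 slide by one rule in both arms.

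The cost is one sentence in the objective and a way of marking the scheduled visit in the data. Returns to the site and slides from all patients are already provided for. The downside is that the saving credited to RDT may look smaller.

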## 4.3.5 Product used

## Paracheck Pf, Cat No. 30301025, M.L.No 635/L, Lot No. 21071, Mfg. Date May 2004, Exp. Date April 2006, Manufactured by Orchid Biomedical Systems, [name].

### Locality

## The study will be conducted in four different Health facilities (HF) in Zanzibar Islands, two in each Unguja and Pemba Islands. The tentative HFs are: Muyuni (Unguja South District), Uzini (Unguja Central), Kinyasini (Pemba, Micheweni District) and Mzambarauni (Pemba, Wete District). Each study site will enrol patients into both study arms.

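### The protocol says its choice of sites will allow MSF's impact to be evaluated, but a non-randomised contrast of two sites with two, without a baseline, cannot support an impact claim

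*Protocol*

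**What the plan says.** After the primary and secondary objectives, the Study objective section adds: "The selection of the study sites will enable an evaluation of the impact of MSF case management intervention since two out of four sites" will by then have had MSF training in clinical diagnosis.

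The rest of the protocol shows where that exposure comes from:

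- The Introduction says "In June 2004 MSF started an intervention in Unguja South and North A district and Wete district in Pemba within Zanzibar archipelago". Annex IV puts this study in February to June 2005, so exposure was settled before the study and outside it.
- The Locality section lists the tentative sites as "Muyuni (Unguja South District), Uzini (Unguja Central), Kinyasini (Pemba, Micheweni District) and Mzambarauni (Pemba, Wete District"). Read against the MSF districts, the exposed sites are Muyuni and Mzambarauni, and the unexposed sites are Uzini and Kinyasini: one of each per island. The protocol does not name the two exposed sites; this follows from the districts.
- The Randomization section allocates only the diagnostic method, by alternating weeks within each site. The Locality section adds that "Each study site will enrol patients into both study arms".
- The Sample size section is built on an assumed 50% reduction from adding RDT. It gives no effect size, power or number for an MSF contrast.

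**The concern.** Evaluating impact means attributing a difference to the MSF programme. That needs at least one of three things: allocation of the exposure, a measurement from before it, or enough exposed and unexposed units for site differences to average out. The protocol has none of them, and no analysis plan could add them later.

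The exposure belongs to the site, so the contrast is between two pairs of clinics. Whatever else distinguishes those clinics, above all the district and the person prescribing, moves with MSF status. If the sentence stands, someone may compare several hundred patients with several hundred, obtain a small p-value and report it as the effect of MSF. The harm would be an unsupported conclusion about a programme, and not merely low power.

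**Working it through.** **1. The plan's own figure.** The Sample size section gives 103 per group. With two arms and four sites, 103 × 2 × 4 = 824, as stated (850 are to be enrolled). This figure is for the RDT comparison; there is none for MSF. The 103 itself cannot be verified, because no control proportion is given, but nothing below depends on how it was obtained.

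**2. Baseline.** No pre-MSF measurement is planned at any site. The only earlier data mentioned are the registration-book checks in the Introduction. They cover South District and adherence to the treatment guideline, so they are not a baseline for the four sites.

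**3. What is tied to MSF status.**

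- District: tied, because MSF works by district.
- Prescriber: tied. One clinician makes both kinds of diagnosis at a site (Randomization), and the Budget lists four prescribers for four sites.
- Island: balanced, with one exposed and one unexposed site on each.
- Transmission: partly observable. Slides from all patients are read centrally (Bioanalytical assays), so parasite positivity will be known by site.

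**4. Permutation floor.** The number of ways to label two of four sites as exposed is C(4,2) = 6.

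- Smallest p: 1/6 = 0.167 one-sided, 2/6 = 0.333 two-sided.
- Matched by island, there are 2 × 2 = 4 labellings. Smallest p: 1/4 = 0.25 one-sided, 2/4 = 0.50 two-sided.
- For comparison, 3 versus 3 sites gives 2/20 = 0.10 two-sided, and 4 versus 4 gives 2/70 = 0.029. Four per group is the first size at which two-sided p < 0.05 is possible.

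**5. Site-level t-test.** This relies on normality with 2 degrees of freedom. Assumptions, not document figures: a 50% prescribing proportion, a between-site SD of 5 to 10 points, and an analysis of the clinical-diagnosis weeks with 103 patients per site.

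- Sampling SD of a site proportion = √(0.5 × 0.5 / 103) = 0.0493, or 4.9 points.
- SD of a site result = √(between-site SD² + 4.93²).
- SE of the difference = SD × √(1/2 + 1/2) = SD.
- Difference needed = 4.303 × SD, where 4.303 is the two-sided 5% critical value.

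| Between-site SD (points) | SD of a site result | Difference needed |
|---|---|---|
| 0 | 4.9 | 21 |
| 5 | √(25 + 24.3) = 7.0 | 30 |
| 10 | √(100 + 24.3) = 11.1 | 48 |

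At a between-site SD of 5 points, power for a true 20-point difference is 36%.

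**6. Patient-level test that ignores site.** With 206 versus 206 clinical-diagnosis patients, the naive SE is √(2 × 0.25 / 206) = 0.0493. The true SE is the SD in the table. The type I error is 2 × [1 − Φ(1.96 × naive SE / true SE)].

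- Between-site SD 5 points: 1.96 × 4.93 / 7.02 = 1.38, type I error about 17%.
- Between-site SD 10 points: 1.96 × 4.93 / 11.15 = 0.87, type I error about 39%.

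**The case against.** The sentence stands apart from the primary and secondary objectives and carries no endpoint, hypothesis or test. How MSF status would be analysed can be left to an analysis plan that is not at hand, and estimates by site are themselves a kind of evaluation. This is fair, and it limits the weight of the point. It does not rescue the claim of impact, because allocation, a baseline and the number of sites are matters of design.

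A reader might infer more than the documents support:

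- *That significance is out of reach.* The floor of 0.33 applies to a permutation test, and none is planned. A t-test on site results could reach p < 0.05, given a very large difference.
- *That a patient-level MSF test is planned.* The protocol names no test for this contrast. Item 6 of the working shows a risk, not a stated intention.
- *That 22 to 43 points would suffice.* Taking 4.303 × 5 and 4.303 × 10 gives 21.5 and 43.0, but omits within-site sampling error. Those are the limits with unlimited patients. More patients do help, but only down to those limits.
- *That MSF status is confounded with everything.* Island is balanced, and the central slides show parasite positivity by site. District and prescriber remain inseparable from it.
- *That the MSF sites had already used RDTs.* The Introduction describes the MSF project as including RDT-aided diagnosis in facilities without microscopy, but does not say that Muyuni or Mzambarauni had used it. If they had, it would be part of the MSF package. The supportable statement is that the contrast may not isolate training.

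**Conclusion.** The sentence claims a property that the design lacks. Exposure was fixed by MSF's districts before the study, there are two exposed and two unexposed sites without a baseline, and the sample size was not set for this contrast.

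The permutation floor (0.33 two-sided, 0.50 matched by island) follows from the number of sites alone. The 30 to 48 points, and the type I error of about 17% to 39% for a test that ignores site, rest on the assumed between-site SD of 5 to 10 points, the 50% prescribing proportion and 103 clinical-diagnosis patients per site.

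It would be wrong to read this as a flaw in the main comparison. Each site contributes to both arms, so RDT plus clinical diagnosis against clinical diagnosis alone is not affected. The point concerns one claim attached to the objectives; it is worth correcting because the claim is causal and invites a misleading analysis.

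**What to change.** Replace the last paragraph of the Study objective section with wording such as: Results will be reported separately for each of the four sites, with prior MSF support shown as a descriptive characteristic of the site. The study is not designed to estimate the impact of the MSF intervention; any comparison by MSF status is exploratory and takes the site as the unit of analysis.

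The cost is one sentence of protocol text, with no added patients, sites or data. The sponsor gives up a claim that the design cannot support.
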